# Effect of acupuncture on lung cancer-related fatigue: study protocol for a multi-center randomized controlled trial

**DOI:** 10.1186/s13063-019-3701-0

**Published:** 2019-11-09

**Keywords:** Acupuncture, Lung cancer, Cancer-related fatigue, RCT, Multi-center randomized controlled trial

## Abstract

**Background:**

Fatigue is one of the primary symptoms in lung cancer, with a prevalence of 88.0% in survivors of cancer, and an even higher prevalence post resection surgery. Effective fatigue control after lung cancer surgery is important for patient recovery and quality of life. Some studies have shown that acupuncture might be effective in treating cancer-related fatigue; however, randomized controlled trials (RCTs) of suitable sample size are limited.

**Method/design:**

This is a multi-center, patient-blinded RCT. A total of 320 eligible patients will be recruited in four centers and randomly assigned to either the acupuncture group or the sham acupuncture group in a 1:1 ratio. Treatment will be given twice per week for 12 sessions. Treatment will be given at acupoints GV20, GV29, CV12, CV6, CV4, and bilateral LI4, LR3, SP6, ST36. The primary outcome will be assessed using the Chinese version of The Brief Fatigue Inventory. The secondary outcomes will be measured using The European Organization for Research and The Treatment of Cancer Quality of Life Questionnaire, and the Hamilton Rating Scale for Depression. The primary outcome will be assessed at all main points (baseline, the 3rd week, the 6th week, and at follow up time points) and the secondary outcomes will be assessed at baseline and the 6th week. Intention-to-treat analysis will be used in this RCT.

**Discussion:**

This trial protocol provides an example of the clinical application acupuncture treatment in the management of lung cancer-related fatigue. If the acupuncture treatment protocol confirms that acupuncture is an effective and safe option for lung cancer-related fatigue, it can be adopted as a standardized treatment.

**Trial registration:**

Chinese Clinical Trial Registry, ChiCTR1900022831. Registered on 27 April 2019.

URL: http://www.chictr.org.cn/showproj.aspx?proj=37823

## Background

Cancer is a worldwide health epidemic with ever increasing morbidity and mortality rates. Partially driven by the modern lifestyle, cancer is currently the second leading cause of death worldwide [1–3]. Lung cancer ranks first in the incidence of malignant tumors in China; about 781,000 people suffer from lung cancer per year [4]. Cancer-related fatigue (CRF) is a common comorbidity of oncological disease, and seriously affects the quality of life and mental health of patients. In 2000, the National Comprehensive Cancer Network (NCCN) guidelines note [5] that CRF is characterized by a feeling of fatigue and lack of energy and includes physical, emotional, and cognitive fatigue. It is persistent and is not relieved through rest. It may be caused by cancer itself or cancer-related treatments, and is not proportional to activity [5, 6]. A study has shown that the prevalence of CRF is 88.0% in survivors of cancer [7]. The respiratory function of patients with lung cancer decreases significantly after lung cancer resection, which can lead to worsening fatigue. Treatment of symptoms may be helpful in lung cancer-related fatigue, such as regulating immunity, treatment of depression, nutritional support, improving sleep, and exercise. Yet there are few effective therapies available for treating CRF. Therefore, it is imperative to find an effective treatment that is without side effects.

Acupuncture therapy has been successfully used to treat many varied diseases for thousands of years. In fact, some research on acupuncture for lung CRF has revealed its advantages [8–10], include relieving symptoms, improving patient quality of life, and delaying the progression of cancer. However, most of these studies are of low value because of flawed methodology, such as inappropriate duration of treatment, sample size, and lack of blinding. The lack of objectivity makes the findings of those reports unreliable.

Faced with the limitations of current research, high-quality evidence is needed to confirm the effectiveness and safety of acupuncture for lung CRF. Therefore, through this proposed multi-center, randomized controlled trial (RCT), we aim to obtain evidence on the use of acupuncture in the treatment of lung CRF. The findings of this trial will provide useful information; this will be shared through publication and will provide an optimal acupuncture treatment protocol for lung CRF.

### Hypotheses

This trial aims to prove that acupuncture is an effective intervention that can relieve fatigue and improve the life quality of patients with lung cancer after lung cancer resection surgery.

### Objectives

The objectives of the study are:
To assess whether acupuncture is cost-effective in improving scores on the Brief Fatigue Inventory-Chinese (BFI-C) and European Organization for Research and Treatment of Cancer Quality of Life Questionnaire (EORTC QLQ-C30), when compared with sham acupuncture.To compare the differences in improvement of mood, measured by the Hamilton Rating Scale for Depression (HAMD), between the intervention group and control group.To determine the influence of the credibility of acupuncture on acupuncture treatment, as assessed by the Credibility of Treatment Rating Scale (CTRS).

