### Recruitment

This multi-center, randomized, sham-controlled, patient and assessor blinded trial will be conducted in the Shanghai Yueyang Hospital of Integrated Traditional Chinese and Western Medicine, Shanghai Municipal Hospital of Traditional Chinese Medicine, Shanghai Chest Hospital, and LongHua Hospital Shanghai University of Traditional Chinese Medicine. Participants of the study will be recruited through the outpatient clinic or inpatient, hospital-based Wechat advertising, and posters in the hospital. Any interested patients will be screened by telephone or on site and consented for the study. After being informed of the details of this RCT, participants will be asked to provide signed informed consent, and deliver it to an independent research assistant. Patients will be randomly divided into two groups: the acupuncture group (*n* = 160) and the sham acupuncture group (*n* = 160). All participants will undergo 6-week treatment with acupuncture (or sham acupuncture) and a series of assessments of CRF, free of charge. Timing of treatment assessments and data collection are as follows in Table 1.

**Table 1 Tab1:** Timing of treatment assessments and data collection

	Study period					
	Enrollment	Baseline	Treatment phase		Follow-up phase	
Timepoint	-1 week	0 weeks	3 weeks	6 weeks	4 weeks	12 weeks
Enrollment						
Eligibility screen	X					
Informed consent	X					
Medical history	X					
Allocation		X				
Interventions						
Acupuncture		X	X	X		
Sham acupuncture		X	X	X		
Assessments						
Primary outcome						
BFI-C		X	X	X	X	X
Secondary outcomes						
EORTC QLQ-C30		X		X		
HAMD		X		X		
Others						
Adverse events		X	X	X		
Patients’ satisfaction				X		
Success of blinding				X		

*BFI-C* Brief Fatigue Inventory-Chinese, *EORTC QLQ-C30* European Organization for Research and Treatment of Cancer Quality of LifeQuestionnaire, *HAMD* Hamilton Rating Scale for Depression

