### Outcome measures

We will assess the primary outcome at baseline, week 3, post treatment (week 6), and at follow up at the 4th and 12th weeks after the end of treatment. Secondary outcomes will be assessed at baseline and week 6.

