### Credibility of Treatment Rating Scale (CTRS)

The CTRS is a scale for assessing the credibility of the acupuncture treatments. It consists of four items and is used to assess the participants as “perceived logic of the treatment,” “confidence in recommending the treatment to their friends who have similar complaints,” “confidence in the treatment to alleviate their complaint,” and “likelihood that the treatment would alleviate their other complaints.” A lower score indicates greater confidence in the received treatment [25, 26].

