### Statistical analysis

Statistical analysis of data will be carried out using SPSS 23.0 software. We will use multiple imputation to address any missing data. An independent statistician, who will be blinded to group allocation, will analyze all data, including those from any participants who drop out during the trial, using the intention-to-treat (ITT) method. Baseline demographics will be analyzed descriptively. Changes in BFI-C will be compared between the two groups as the primary analysis, using repeated measures analysis of variance (ANOVA (general linear model)). For the secondary outcomes, scores on the QLQ-C30, HAMD, and CTRS will be compared between the two groups using Student’s *t* test or the Wilcoxon rank-sum test. All reported *P* values will be two-sided, and a *P* value of less than 0.05 will be considered statistically significant. The mean difference and confidence intervals at the 95% level will also be calculated using SPSS.

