## Discussion

Fatigue is a typical symptom that is common in lung cancer and can seriously affect a patient’s quality of life and emotional health [29, 30]. CRF is a common condition that occurs at different stages of oncological disease (after surgery, treatment with target therapy, etc.) [29–31]. With the development of complementary and alternative medicine, more and more patients with cancer tend to choose acupuncture as a main treatment to treat fatigue. Recently, several studies have shown that acupuncture can effectively improve the symptoms of CRF [32–36]. However, there is currently a lack of multi-center, large-sample, sham-controlled, RCTs in CRF [29, 37]. In this study protocol, we designed a randomized, multi-center, sham-controlled, patient and assessor blinded trial (Additional file 1). If the protocol confirms that acupuncture is effective and safe, it can be implemented for relieving CRF and improving quality of life in patients with lung cancer.

Because of the nature of acupuncture, there are many factors that can affect the clinical outcomes, including individual differences, needle insertion techniques and duration of the sessions. Our study protocol is based on literature from textbooks and relevant reports, and on our previous clinical experience. Traditional acupoints will be selected for treatment (GV20, GV29, CV12, CV6, CV4, and bilateral LI4, LR3, SP6, and ST36). Another advantage is that the same trained acupuncturists will implement a standardized protocol for point selection and for the needle insertion, minimizing factors that might affect the clinical outcomes. The nature of acupuncture treatment made double-blinding impossible, but our design incorporating sham acupuncture allows blinding of the patient and assessor. Only the acupuncturist will know the treatment allocation, but they will know nothing about the results, and assessors do not know the treatment allocation before and after the evaluation of treatment efficacy, thus avoiding the potential for bias. Another innovation in this study protocol is the use of the CTRS to assess the influence of the patients’ perceptions of the credibility of acupuncture on acupuncture treatment.

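### Objective 3 asks how treatment credibility influences the acupuncture treatment, but the only stated CTRS analysis compares CTRS scores between arms, and when the CTRS is taken is unresolved

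*Protocol article*

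**What the plan says.** The third item under Objectives is "To determine the influence of the credibility of acupuncture on acupuncture treatment, as assessed by the Credibility of Treatment Rating Scale (CTRS". The Discussion repeats the aim and presents as an innovation the "use of the CTRS to assess the influence of the patients’ perceptions of the credibility of acupuncture on acupuncture treatment".

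The section on the CTRS describes four items and how the score is read: "A lower score indicates greater confidence in the received treatment". It gives no assessment time.

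Statistical analysis takes the CTRS up in its sentence on secondary outcomes: "scores on the QLQ-C30, HAMD, and CTRS will be compared between the two groups", by Student's t test or the Wilcoxon rank-sum test. The primary analysis, a repeated measures ANOVA of BFI-C change, names no CTRS term.

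On timing, Recruitment says "Timing of treatment assessments and data collection are as follows in Table 1". That table has rows for the BFI-C, QLQ-C30, HAMD, adverse events, "Patients’ satisfaction" (week 6 only) and success of blinding, but no row named CTRS. Outcome measures says "Secondary outcomes will be assessed at baseline and week 6". The Abstract and Table 1 name only the QLQ-C30 and HAMD as secondary outcomes.

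**The concern.** An objective about the influence of credibility needs an analysis in which credibility and outcome appear together. The article states an objective, an analysis and a schedule for the same instrument, and the three do not fit. If the plan is followed as written, the trial can report whether the two procedures were equally believable. It cannot report whether patients who found their treatment more credible improved more, or whether the effect of acupuncture depends on credibility.

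Timing decides how useful the data will be. An unseen analysis plan can add a model. It cannot supply an early rating that was never scheduled.

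**Working it through.** **1. Objective against analysis.** Let C be the CTRS score, A the arm and Y the week-6 change in BFI-C.

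- The stated test concerns mean(C | A = acupuncture) − mean(C | A = sham). Y does not enter it.
- The objective concerns c and d in Y = a + b·A + c·C + d·(A×C). Neither is determined by the difference in mean C.

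No section relates the CTRS to the BFI-C, whether as covariate, interaction, subgroup, correlation or mediator.

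**2. Illustration with assumed values.** The article gives no CTRS figures, so all of these are assumptions except the 0.35 and the 133: 133 per arm, CTRS mean 10 and SD 3 in both arms, Y = −2 − 0.35·A + s·(C − 10) + error with SD 0.9. A positive s means that greater confidence (a lower score) goes with a larger fall in fatigue.

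- One simulated data set with s = 0.15 and CTRS means set equal gave p = 1.00 for the planned between-arm test and r = 0.43 between CTRS and BFI-C change.
- The expected correlation is r = 3s / √(9s² + 0.9² + 0.35²/4).
- s = 0: r = 0. s = 0.05: 0.15/√0.863 = 0.16. s = 0.15: 0.45/√1.043 = 0.44. s = 0.30: 0.90/√1.651 = 0.70.

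The planned test returns the same result across this whole range, because s plays no part in it. The values of r are consequences of the assumed s, not estimates for this trial.

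**3. Timing, side by side.**

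- Table 1: no row named CTRS, and CTRS is absent from its abbreviation note.
- Statistical analysis with Outcome measures: if the CTRS is a secondary outcome, it is taken at baseline and week 6.
- Abstract and Table 1: the CTRS is not listed as a secondary outcome.
- CTRS section: the score concerns treatment already received. This fits poorly with baseline, because Randomization and allocation concealment reveals allocation only after the baseline assessments. A between-arm difference at that point could only be chance.
- Week 6 comes after all 12 sessions. One CTRS item asks about confidence that the treatment relieves the complaint, and by then the patient may already have felt a result.

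**4. What an added model could show.** The article's own sample size reproduces. The pooled SD is √((1.03² + 1.00²)/2) = 1.015, and n = 2·(1.96 + 0.84)²·1.015²/0.35² ≈ 132 to 133 per group; Welch power at 133 is 80.0%. Take 1.015 as the residual SD (an assumption) and express C in SD units:

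- Slope in one arm: SE = 1.015/√133 = 0.088, so the 95% CI is about ±0.17 BFI-C points per SD of CTRS.
- Difference in slopes: SE = 1.015·√(2/133) = 0.124. The difference detectable with 80% power is 2.80 × 0.124 ≈ 0.35. With all 160 per arm it is 2.80 × 1.015·√(2/160) ≈ 0.32.

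The interaction is therefore detectable only if one SD of CTRS changes the treatment effect by about as much as the whole planned effect of 0.35. The model has to be exploratory.

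**The case against.** Four points count on the other side.

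- **The data may well be collected.** In the last block of Table 1 the rows run adverse events, satisfaction, blinding. The text sections run safety, CTRS, blinding. Satisfaction has no section of its own, and the CTRS stands in its place. The "Patients’ satisfaction" row at week 6 may be the CTRS under another label. The route through the secondary outcomes also gives a week-6 value. A reader might infer from the missing row that no CTRS data will exist; the documents do not support that. What stands is that nothing states the link, so the timing needs to be reconciled.
- **A model can be added later.** If the CTRS is collected, each patient has both scores, and the article does not say that the between-arm test is the only CTRS analysis. An analysis plan might contain more. This softens the point but does not remove it: the article names an analysis for this instrument, and that analysis answers a different question.
- **The between-arm test is not irrelevant.** The objective is loosely worded. If it means whether unequal credibility could explain a difference between arms, similar CTRS scores would bear on it. That is a reason to keep the test, but it still leaves credibility unrelated to outcome.
- **Baseline is not useless.** Most of the four items could be asked prospectively, and such a rating would precede the outcome. A reader might infer that cause and effect are reversed in this design. The documents do not show that: a baseline rating may be intended, and at week 6 an influence of improvement on the rating is a risk, not a fact. The reference to treatment already received counts against a baseline rating but does not settle the matter.

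**Conclusion.** The mismatch holds: one of three stated objectives, repeated in the Discussion as a strength, is not answered by the analysis stated for it. The timing of the CTRS is unresolved. That is different from showing that the data are absent or the direction of influence reversed, and neither of those should be concluded.

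The documents give no CTRS mean, SD or correlation with the BFI-C, so no bias can be put in figures; the correlations in the illustration only show that the planned test does not respond to the quantity of interest. The primary BFI-C analysis, the sample size and the error rate are untouched. The point is worth correcting because the remedy is cheap, and an early rating cannot be recovered afterwards.

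**What to change.** 1. Name the CTRS in Table 1, with a rating after the first or second session in both arms and before the week-3 BFI-C. State whether the satisfaction row is the CTRS, and whether the CTRS counts as a secondary outcome.
2. Add one exploratory model of week-6 BFI-C change with arm, early CTRS and CTRS-by-arm. Report the slope in each arm with a 95% CI. State that the CTRS is not randomised, so its slope may be confounded, and that power for the interaction is low.
3. Keep the between-arm CTRS comparison, described as a check on the sham.
4. If no early rating is added, reword objective 3 and the matching Discussion sentence as a comparison of credibility between arms.

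The cost of steps 1 to 3 is a four-item form at an existing session and one extra model, with a small burden for patients. Step 4 costs only a change of wording, but it gives up the question of influence.

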## Methods/design

### Study design

We propose a multi-center, randomized, sham-controlled, patient and assessor blinded trial. The trial commence in four centers after ethical approval has been obtained from the Institutional Review Board. The clinical trial is designed and reported following the Consolidated Standards of Reporting Trials [11] and Standards for Reporting Interventions in Clinical Trials of Acupuncture guidelines [12]. Eligible patients will be randomly divided into the acupuncture group and the sham acupuncture group in a 1:1 allocation ratio. All participants will provide signed informed consent before proceeding with the trial. The flow chart of the study process is shown in Fig. 1.

**Fig. 1 Fig1:**
[figure not shown]
Flowchart of the study process. BFI-C, Brief Fatigue Inventory-Chinese; QLQ-C30, European Organization for Research and Treatment of Cancer Quality of Life Questionnaire; HAMD, Hamilton Rating Scale for Depression

### Sample size

The sample size calculation was based on change in BFI-C scores. According to previous studies [13], we assume the change is − 2.35 in the acupuncture group and − 2.0 in the sham-acupuncture group; therefore, the mean difference between two group is 0.35 with standard deviations of 1.03 and 1.00, and a sample size of 133 per group will provide 80% power to reject the null hypothesis with a significance level of 0.05, using a two-sided, two-sample, unequal-variance *t* test. Allowing for a dropout rate of 20%, a total of 320 participants should be recruited for this trial.

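### 320 recruited with 20% dropout leaves 128 per group, not the 133 per group the protocol says it needs for 80% power

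*Protocol article*

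**What the plan says.** The Sample size section of the protocol article works from change in BFI-C and takes 0.35 as the difference between the groups, the two SDs being 1.03 and 1.00. On that basis it concludes that "a sample size of 133 per group will provide 80% power to reject the null hypothesis". The test behind this claim is a Welch-type t test, two-sided at the 5% level. The dropout allowance follows in a separate sentence: "Allowing for a dropout rate of 20%, a total of 320 participants should be recruited for this trial".

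The abstract repeats the total: "A total of 320 eligible patients will be recruited in four centers". The Recruitment section splits it into 160 per group. The formula used to get from 133 per group to 320 is not shown.

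**The concern.** A dropout rate is normally a share of those recruited. If a fifth are lost, four fifths remain, so the number needed has to be divided by 0.8. The step from 266 to 320 is an increase of about one fifth, which is what multiplying by 1.2 gives. That allowance is too small for the dropout rate named.

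What is at stake is the accuracy of a published design claim. The 133 per group only just reaches 80% power, so there is no slack to absorb the shortfall. If dropout is as high as the protocol itself expects, the trial will not have the power stated for it.

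**Working it through.** **Inputs**, all from the Sample size section unless noted:

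- difference in mean change: 0.35
- standard deviations: 1.03 and 1.00
- two-sided alpha 0.05, power 80%, unequal-variance t test
- needed per group: 133 (266 in total)
- dropout: 20%
- total recruited: 320, as 160 per group (Recruitment section)

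**Step 1. Reproduce the 133.** The normal-approximation formula is

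n = (z₀.₉₇₅ + z₀.₈₀)² × (SD₁² + SD₂²) / difference²

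= (1.960 + 0.842)² × (1.03² + 1.00²) / 0.35² = 132.05 with unrounded quantiles, rounded up to 133.

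Power from the noncentral t distribution with Welch degrees of freedom is 79.996% at 133 per group. The 133 is therefore sound, and only the dropout step needs attention.

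**Step 2. Apply the stated dropout to the stated total.**

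- 320 × 0.8 = 256 completers, or 128 per group
- shortfall in completers: 133 − 128 = 5 per group, 266 − 256 = 10 in total

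**Step 3. Total needed to keep 133 per group.**

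- 133 / (1 − 0.20) = 166.25, rounded up to 167 per group, 334 in total
- rounding only the total: 266 / 0.8 = 332.5, rounded up to 333
- shortfall in recruitment with equal groups: 334 − 320 = 14 (14/320 = 4.4%)

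**Step 4. Look for a route to 320.**

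| Starting point | Divide by 0.8 (total) | Multiply by 1.2 (total) |
|---|---|---|
| 132 per group | 330 | 316.8 |
| 133 per group | 332.5 | 319.2 |
| 134 per group | 335 | 321.6 |

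A one-sided test would need 105 per group, or 210/0.8 = 262.5 in total. Dividing by 0.8 never gives 320. Multiplying does: 133 × 1.2 = 159.6, rounded up to 160 per group, 320 in total.

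**Step 5. Size of the effect** (same Welch t test, completers only).

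| Completers per group | Power |
|---|---|
| 128 | 78.5% |
| 133 | 80.0% |
| 160 (no dropout) | 86.7% |

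- Difference detectable with 80% power at 128 per group: 0.35 × √(133/128) = 0.357
- Highest dropout at which 320 still leaves 266: 1 − 266/320 = 0.169, or 16.9%

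**The case against.** Five points can be made for the plan.

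- **The 1.2 multiplier is not printed.** This is correct, and the explanation should be read as an inference. The mismatch does not depend on it: 320 recruited, 20% lost and 133 per group remaining cannot all hold.
- **The Statistical analysis section plans intention-to-treat with multiple imputation, so dropouts still contribute.** This stands in part. Baseline BFI-C should be available for everyone randomized, and some dropouts will have a week-3 score. Under missing at random, the approximate effective size per group is 1/[(1 − r²)/128 + r²/160], where r is the correlation of baseline score with change. It is 128 at r = 0 and reaches 133 at about |r| = 0.43. If half the dropouts have week-3 data, replacing 160 by 144, it takes a correlation of about 0.58 between the week-3 data and the outcome. These correlations and the half share are assumptions, since the document gives none. Imputation might therefore close the gap, but the sample size calculation takes no credit for it and makes a separate dropout allowance instead.
- **The 20% may cover the whole trial.** The primary outcome is the change at week 6, while follow-up runs to 12 weeks after treatment. If no more than 16.9% are lost by week 6, 133 per group remain. The Sample size section says nothing of the kind and applies the 20% directly to the number needed for the primary outcome.
- **The planned primary analysis is repeated measures ANOVA, not a t test.** True, so 78.5% is not the power of that analysis. The printed 80% claim is for the t test, and that is the claim checked here.
- **The effect is small.** It is: about 1.5 percentage points of power, which matters little beside the uncertainty in the assumed difference and standard deviations. This bears on how much weight the point deserves and leaves the printed figures inconsistent.

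**Conclusion.** The concern holds. The 133 per group is correct, but the dropout allowance built on it is not: at the stated 20%, recruiting 320 leaves 128 per group. The stated t test then has 78.5% power, and the difference detectable with 80% power is 0.357. Keeping the stated 80% at 20% dropout would take 334 participants.

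This rests on the 20% being a share of those recruited, falling evenly on the two groups and lost before the week-6 assessment, and on power being counted for completers with no gain from imputation. The error is modest and does not threaten the design, but the sentence is wrong as written and easy to correct.

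**What to change.** Keep 320 participants and correct the dropout sentence in the Sample size section in one of two ways:

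- state that with 20% dropout 128 per group are expected to complete, giving about 78.5% power for the two-sample t test on completers; or
- state that 320 participants give 80% power with dropout of up to about 16.9%.

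It would also help to say by which time point the dropout is counted. Either wording costs one sentence and a slightly less favourable figure, with no extra patients and no change to the analysis.

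If both the 80% power and the 20% dropout are to stand, the total has to rise to 334 (167 per group), which costs 14 more participants and matching changes in the abstract and the Recruitment section.
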